## Abstract

**Background:**

The Vaccine Assessment using Linked Data (VALiD) trial compared opt-in and opt-out parental consent for a population-based childhood vaccine safety surveillance program using data linkage. A subsequent telephone interview of all households enrolled in the trial elicited parental intent regarding the return or non-return of reply forms for opt-in and opt-out consent. This paper describes the rationale for the trial and provides an overview of the design and methods.

**Methods/Design:**

Single-centre, single-blind, randomised controlled trial (RCT) stratified by firstborn status. Mothers who gave birth at one tertiary South Australian hospital were randomised at six weeks post-partum to receive an opt-in or opt-out reply form, along with information explaining data linkage. The primary outcome at 10 weeks post-partum was parental participation in each arm, as indicated by the respective return or non-return of a reply form (or via telephone or email response). A subsequent telephone interview at 10 weeks post-partum elicited parental intent regarding the return or non-return of the reply form, and attitudes and knowledge about data linkage, vaccine safety, consent preferences and vaccination practices. Enrolment began in July 2009 and 1,129 households were recruited in a three-month period. Analysis has not yet been undertaken. The participation rate and selection bias for each method of consent will be compared when the data are analysed.

**Discussion:**

The VALiD RCT represents the first trial of opt-in versus opt-out consent for a data linkage study that assesses consent preferences and intent compared with actual opting in or opting out behaviour, and socioeconomic factors. The limitations to generalisability are discussed.

**Trial registration:**

Australian New Zealand Clinical Trials Registry ACTRN12610000332022

## Background

Options for consent that are available for health and medical research involving human subjects are: no consent, using either identifiable or non-identifiable data; opt-in consent, where each person is informed about the research and their consent is sought; and opt-out consent, where each person is informed about the research and included unless they indicate an unwillingness to participate [1]. A request for consent may be either project-specific, extended (for future research projects) or broad authorisation for research use [2]. Under the opt-in approach, the subject's failure to act leads to non-inclusion; but 'non-participation' may not stem from a meaningful decision and may reflect a lack of contemplation or intention [3]. Under the opt-out approach, inclusion in research may largely depend on individuals' inertia; therefore, the true proportion of people who do not wish to participate may be understated [4].

In Australia, the *National Statement on Ethical Conduct in Human Research *[2] guides Human Research Ethics Committees (HRECs) to require opt-in consent under most circumstances. However, health information can be used in the conduct of specific activities (including research of various types) without a subject's permission 'provided an assessment is made by an HREC that the research and other activities are, on balance, substantially in the public interest' [5]. Data linkage is one such specific activity [2], defined as 'the bringing together, from two or more different sources, data that relate to the same individual, family, place or event' [6].

The development in recent decades of integrated electronic administrative healthcare databases has enabled sophisticated and powerful population-level data linkage studies on the factors influencing health and wellbeing, and health services evaluation [7-10]. Privacy advocates have perceived these developments as a potential threat to privacy, sparking an increase in the rigour and complexity of the privacy framework in Australia and associated regimens of HREC submissions [5,8,11-14]. Threats to privacy are minimised when data linkage adheres to the best practice protocol [15], whereby strict separation of individual demographic identifiers from clinical health information is maintained during and after the linkage process, ensuring researchers never receive personal identifiers and data custodians never exchange identifiable health data [6,15]. Despite the availability of privacy-conserving linkage protocols, some data custodians still require each individual's opt-in consent for release of data [11,16], with severe adverse consequences for the quality and validity of research. Holman *et al*. suggest that when a system of consent leads to participation rates of less than 90%, the information available for the research becomes biased [11].

Several cross-sectional surveys and focus groups conducted internationally [17-22] and in Australia [5,23] have shown that the public has a strong preference to be asked for consent for health and medical research, including for data linkage studies [5,20,22]. There are some notable exceptions: in two cross-sectional surveys conducted in the United Kingdom [24] and Australia [25], the majority of the public did not consider the inclusion of identifiable health data in a cancer registry and birth defects registry without consent to be an invasion of privacy and expressed support for statutory case registration. In terms of consent to data linkage, there are no studies that have compared the numbers and characteristics of participants enlisted under opt-in and opt-out conditions using a well-designed Randomised Controlled Trial (RCT). While there are RCTs that relate to other aspects of medical research [26-30], the extent of participation has varied widely, ranging from 48%-85% in the opt-in arm and 59%-100% in the opt-out arm, and all but one [28] had a small sample size or flawed methodology [26,27,29,30] (Table 1). Only two RCTs [26,30] are relevant to data linkage in that participation required no effort on the part of the subject in terms of clinic attendance or involvement in disease screening, and there were no follow-up reminders, which are not economically or logistically feasible for large population-level studies [11].

**Table 1 T1:** RCTs of opt-in and opt-out consent

Study population and purpose	**Parents in a health district of the UK were asked for consent for inclusion of low birth-weight infants on a register for the purpose of monitoring disability in children **[26]	**Mothers in the US were asked for consent for inclusion of infants at high risk to participate in a clinical trial of primary follow-up care **[27]	**Angina patients in two general practices in the UK were asked for consent to be involved in clinical research **[28]	**Patients aged 50-74 years in a general practice in Australia were asked to consent to testing decision aids for the screening of colorectal cancer **[29]	**Cancer patients in the Netherlands who had undergone primary surgery were asked for consent for the storage of excised tissue for future research purposes **[30]
Sample size randomised (n)	Opt-in: 39 Opt-out: 30	Opt-in: 32 Opt-out: 25 (3 were excluded as they did not receive the allocated intervention)	Opt-in: 252 Opt-out: 258	Opt-in: 92 Opt-out: 60	Opt-in: 60 'Opt-out plus': 73 Control group (standard opt-out): 131
Mode of invitation	Verbal information, letter and reply slip given by a nurse prior to an infant's discharge from hospital	Verbal information and reply form given by a nurse within 24-48 hours of delivery. The opt-out form was shortened to include only specific disclosures that are appropriate for low risk research	Letter, information leaflet and reply card sent from a doctor	Letter sent from a doctor (plus reply card for the opt-in arm only)	Verbal information, specific information leaflet and reply form given by a doctor/nurse. The control group was only given a routine hospital leaflet and did not receive verbal information
Mode of response	Reply-paid slip	Reply form was collected from the mother	Reply card or telephone	Telephone or email (or reply-paid card for the opt-in arm)	Reply-paid form. The control group leaflet instructed patients to opt out by informing their doctor
Reminder letter	No	No	After two weeks for the opt-in arm only	No	No
Time to respond	Not stated	Prior to discharge from hospital. Once a mother reached a decision, an interview occurred within the next 24 hours (usually 2 hours)	Opt-in: Not stated Opt-out: patients could opt out verbally when telephoned after two weeks	Not stated	One month
Participation rate	Opt-in: 79% Opt-out: 97%	Opt-in: 75% Opt-out: 91%	Opt-in: 48% Opt-out: 59%	Opt-in: 51% Opt-out: 90%	Opt-in: 85% 'Opt-out plus': 97% Standard opt-out: 100%
Recruitment rate	Not applicable	Face-to-face interview Opt-in: 81% Opt-out: 82%	Clinic attendance Opt-in: 38% Opt-out: 50%	Telephone survey Opt-in: 47% Opt-out: 67%	Postal and telephone survey Opt-in: 93% and 52% 'Opt-out plus': 93% and 51% Standard opt-out: 88% and 47%
Evidence of selection bias	Not stated	Modest differences were found. Subjects recruited in the opt-in arm were older, more likely to be married and undergo a vaginal delivery than subjects in the opt-out arm	Subjects recruited in the opt-in arm were healthier and had less risk factors for coronary disease than subjects in the opt-out arm	Subjects recruited in the opt-in arm were more likely to prefer an active role in decision making than subjects in the opt-out arm	Subjects recruited in the opt-in arm were similar in age, sex, education and type of cancer to the 'opt-out plus' arm. The control group was similar, except that women were over-represented
Design flaws	Small sample size, non-random allocation and no mention of whether blinding was used	Small sample size and the collection of reply forms is resource-intensive and impracticable on a large scale	None evident	Small sample size and non-parallel design	Small sample size and no mention of whether blinding was used

There has been relatively little research on non-participants in RCTs because of problems in obtaining ethical approval [31,32]. Only two RCTs have elicited the intent behind the return or non-return of forms for subjects in the opt-in and opt-out trial arms by means of a face-to-face interview [27], or postal and telephone survey [30]. We designed a large RCT of opt-in and opt-out consent for a proposed data linkage study into adverse events following immunisation. All eligible subjects were included in the RCT without their prior consent being sought, which necessitated a consent waiver from the approving HREC. Our justification for not obtaining consent was that if prior consent were sought it would lead to a selection bias in the study sample. In order to study reasons for participation and non-participation, we followed up the trial with a telephone interview aimed at all randomised subjects, whether or not they had indicated consent to the data linkage study.

### Purpose

#### Primary objective and hypotheses

To determine which method of obtaining parental consent (opt-in or opt-out) provided the highest participation rate for a population-based childhood vaccine safety surveillance program using data linkage.

The following Null hypotheses will be tested:

(1) There is no difference in the participation rate for the opt-in and opt-out method, that is, the proportion of parents who opt in by return of a reply form (or telephoning or email) and the proportion who do not opt out.

(2) Neither the opt-in nor opt-out method of consent will result in parental participation greater than 90%.

#### Secondary objective and hypotheses

To examine consent preferences, and attitudes and knowledge about vaccine safety, data linkage and vaccination practices by means of a structured telephone interview of all randomised subjects.

The following Null hypotheses will be tested:

(1) There are no differences in the motivations and barriers given for the return/non-return of the reply form by subjects who consented, or did not consent, in the opt-in arm compared with subjects in the opt-out arm.

(2) There are no differences in consent preferences, and attitudes and knowledge about vaccine safety, data linkage, vaccination practices and socio-demographics of subjects who consented, or did not consent, in the opt-in arm compared with subjects in the opt-out arm.

## Methods and Design

### Study design and flow

This was a single-centre, stratified (firstborn versus subsequent births), single-blind, parallel-group RCT conducted in the Women's and Children's Hospital (WCH), a tertiary referral centre in metropolitan Adelaide, the capital city of South Australia (SA) with a population of about 1.19 million in 2009 [33]. Approximately 25% of all South Australian babies are delivered at the hospital [34]. The study population consisted of parent(s) of every consecutive child born in a three-month period: from July 27, 2009, to October 25, 2009, inclusive. Data listings of eligible live births were provided by the SA Department of Health (SA Health) utilising the electronic patient management system (*HOMER™*). The RCT received ethical approval from the Children, Youth and Women's Health Service (CYWHS) HREC (Reference: REC2087/7/11) who granted a waiver of the usual requirement of individual, fully informed consent to participate in an RCT and allowed the limited disclosure to subjects of the true purpose of the trial.

### Inclusion and exclusion criteria

Selection of subjects was based on the hospital records of mothers who met the study eligibility requirements (Table 2). Further exclusions were made on a case-by-case basis if an audit of the medical record revealed that the mother was incarcerated, mentally incapacitated, or the baby had been adopted or placed into foster care. Since infant (and maternal) deaths following a mother's discharge are not routinely captured in the hospital's patient management system, the South Australian Births, Deaths and Marriages Registration Office was engaged to conduct weekly searches to identify any deaths which might have occurred prior to randomisation and, where identified, the mother was excluded from the trial. Weekly searches for deaths continued until parents exited the interview. The flow of subjects in this study is shown in Figure 1.

**Table 2 T2:** Eligibility criteria and rationale

Criterion	Rationale
*Inclusion criteria*	
Mothers who had a live and surviving birth at the WCH.	A birth must be viable and surviving to enable data linkage of immunisation encounters at two months and hospital admissions after birth.
Mother's age was equal or above 18 years.	This is the age accepted by HRECs where informed consent can be given by an individual.
Mother was a resident of SA.	The data linkage will involve only South Australian children whose immunisation encounters will be linked with admissions to a South Australian hospital. Cross-jurisdictional migration will be unaccounted for i.e., if a family moves interstate after the birth or an infant is admitted to an interstate hospital.
*Exclusion criteria*	
Maternal death, stillbirth or neonatal death. In the instance of twins or triplets, if one died, the mother was excluded.	To avoid causing distress to a bereaved family.
Infant stays in the NICU of 2 weeks or longer.	To avoid causing distress to a family dealing with issues of infant illness and prematurity.
Home births and births that occurred at other hospitals and were subsequently managed at the WCH.	To ensure each mother had received the same type of care prior to discharge and data were available in the hospital patient management system for all variables of interest.

**Figure 1 F1:**
[figure not shown]
**Flow diagram of opt-in compared with opt-out trial**.

### Sample size

The primary outcome of interest was a comparison of the parental participation rate in each arm. To detect an effect size difference of 10% (assuming 80% in the opt-out arm and 70% in the opt-in arm) using a two-tailed test at the 5% level with power of 80% we required 313 subjects in each arm (total 626 subjects). A further 10% inflation allowed for the stratified design of randomisation for the pre-specified confounder of firstborn status. Thus, the sample size for the primary outcome required 344 subjects in each arm: a total of 688 subjects. However, important secondary outcomes of interest related to the recruitment of parents for the subsequent telephone interview. The sample size required for the secondary outcome was 544 subjects in each arm: a total of 1,088 subjects.

### Randomisation and blinding

The unit of randomisation was the mother who was randomly allocated, by date order of confinement, to the opt-in and opt-out arm in the ratio 1:1. The randomisation schedule was stratified by firstborn status (first live and surviving birth versus subsequent births). It used randomly permuted blocks of sizes 2, 4, 6 and 8 and was created using the program ralloc [35] in Stata statistical software [36]. We stratified on firstborn status because we judged that a parent's likelihood of participating in a data linkage study of childhood vaccine safety, and their attitudes towards vaccination and vaccination practices, could be influenced by previous experience of infant immunisation, especially if an adverse event occurred following immunisation.

The trial was single-blinded: parents were unaware that two types of consent were being compared, but were aware of the data linkage study. Blinding was not appropriate for the two researchers [[name], JW] who conducted interviews since the interview structure required knowledge of whether the parent had, or had not, returned the reply form. For the analysis and reporting, the primary outcome will be assessed by one researcher who will be blind to allocation.

### Intervention and follow-up

All households received a cover letter (addressed to the mother), an information leaflet and a reply-paid form, with different formats according to allocation to the opt-in or the opt-out arm (Figure 1). The study material invited parents to be part of a 'Vaccine Data Linkage Study' in order to investigate data linkage as a new way of checking for rare reactions to vaccines by looking at large numbers of children. Parents were asked for permission to link infants' two-month vaccination records with any hospital visits occurring in the month following vaccinations. The study invitation was mailed after randomisation at six weeks post-partum; its arrival was timed to advise parents of the study one to two weeks prior to the scheduled two-month vaccinations. Parents in the opt-in arm were instructed to return a reply form to signal willingness to participate in data linkage; whereas parents in the opt-out arm were informed they would be included unless they returned a reply form to refuse consent. Telephone or email response was also accepted. No follow-up reminder letters were sent, to make the participation rate - the response to one invitation - relevant to large population data linkage studies. The cut-off time for data to be included in the estimation of the participation rate at 10 weeks post-partum included the first day of the 11th week to allow for internal hospital postal delays, giving all parents four weeks to respond. The telephone interview occurred when infants reached 10 weeks of age, corresponding with one to two weeks after administration of the two-month vaccinations to enable data collection on vaccination practice and experience of adverse events.

### Data management

All data collection and interviews occurred at the study centre. A database was developed to manage the study flow and follow-up of subjects, the mail-out of study invitation material, and transcription of telephone interview responses from paper booklets into electronic format. All data were kept securely on a non-networked computer. File back-ups and associated paperwork were stored in a locked filing cabinet, as required by relevant guidelines for the ethical conduct of research.

### Outcome assessment

The primary outcome at 10 weeks post-partum was the proportion of parental participation in each arm, as indicated by the respective return or non-return of a reply form (or via telephone or email response). Secondary outcome data, including socio-demographic characteristics, were captured from the hospital's patient management system and at the subsequent telephone interview at 10 weeks post-partum. These included: 1) the interviewee's age, gender, marital status, country of birth, main language at home and level of education; 2) the mother's age, marital status, country of birth, Indigenous status and firstborn status of the infant; and 3) the household size, composition, annual income, Socio-Economic Indexes For Areas (SEIFA) Index of Relative Socio-Economic Disadvantage (IRSD) [37] and location (major cities or other). The IRSD and location measures were derived from postcode of usual residence.

The study invitation material and telephone survey were designed and administered according to recommended principles [38,39]. They were initially piloted on a small number of academic staff, and then further modified and refined through piloting on a convenience sample of 20 subjects similar to the study's target group: parents of young children. The pilot groups were re-utilised by the study team for training purposes to develop skills in the delivery of the telephone interview. The survey collected information on the parent's recall of the study and its purpose, reasons for the return or non-return of the reply form, consent preferences, understanding of data linkage and the level of trust in its protection of privacy. The survey also canvassed attitudes towards vaccination in terms of its public health benefit, safety, and effectiveness; vaccination practices; experiences of minor and serious infant illness and the likelihood of being vaccine-related; and socio-demographics measures. Questions relating to consent preferences [20] and perceptions about the safety and effectiveness of vaccines [20,40] were derived from published telephone surveys to assist in comparison with similar studies.

The interview schedule was designed to be pragmatic to optimise response rates. While the researchers endeavoured to interview the parent (either mother or father) who had opted in or opted out as identified by name on the reply form, this was not always possible even with multiple call-backs. In such instances, the other parent, if available, was interviewed as a proxy. For households who neither opted in nor opted out, the interviewers had no knowledge of which parent, if any, had read the study invitation material. The first parent to answer the telephone was invited, as there was no basis for preferentially interviewing one parent over the other.

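### Which parent is interviewed depends on reply status, so respondent selection is nearly aliased with arm when consenters (or non-consenters) are compared on interview data

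*Protocol article*

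**What the plan says.** **Who is interviewed (Outcome assessment).** For households that replied, "the researchers endeavoured to interview the parent (either mother or father) who had opted in or opted out as identified by name on the reply" (that is, on what the household sent back). If that parent could not be reached despite repeated calls: "In such instances, the other parent, if available, was interviewed as a proxy". For households that did not reply, "the interviewers had no knowledge of which parent, if any, had read the study invitation material", and so: "The first parent to answer the telephone was invited, as there was no basis for preferentially interviewing one parent over the other".

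**What a reply means (Intervention and follow-up).** "Parents in the opt-in arm were instructed to return a reply form to signal willingness to participate in data linkage". In the opt-out arm the form is returned to refuse, and silence counts as inclusion.

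**What is compared (Secondary objective and hypotheses).** The first secondary null concerns reasons for returning or not returning the form, by consent status, between arms. The second concerns vaccination practices, preferences, attitudes and knowledge, and also "socio-demographics of subjects who consented, or did not consent, in the opt-in arm compared with subjects in the opt-out arm".

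**What is adjusted for (Analysis plan).** Simple tests, then generalised linear models with socio-demographic adjustment where appropriate. Respondent role, proxy status and the rule by which the respondent was chosen are not mentioned. Among the socio-demographics collected are "the interviewee's age, gender, marital status, country of birth, main language at home and level of education". Mother-level and household-level variables are listed separately.

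**The concern.** The secondary hypotheses condition on consent status and then compare arms. Consent is defined by reply status in opposite directions in the two arms, and reply status also decides how the respondent is found. An opt-in consenter household is therefore normally represented by the parent who signed. An opt-out consenter household is represented by whoever answered the telephone, who may not be the parent who dealt with the letter.

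If the two rules reach different mixes of parents, a gap in knowledge of data linkage, trust, consent preference, or the interviewee's gender or education could arise from the interview procedure. It could then be read as evidence that the consent methods enlist different people. Adjusting for the interviewee's socio-demographics deals with only part of this. Gender can be adjusted for, but whether the respondent made the decision cannot. The limitations in the Discussion cover honesty of answers, limited English and late forms prompted by the interview, but not this.

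**Working it through.** **1. Map the rule onto the comparison cells.**

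| | Opt-in arm | Opt-out arm |
|---|---|---|
| Consenters | replied: named parent, else proxy | did not reply: first to answer |
| Non-consenters | mostly did not reply: first to answer | replied: named parent, else proxy |

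Within each row, arm and selection rule almost coincide. The overlap is not perfect: replies by telephone or email, proxies, and forms prompted by the interview blur it.

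**2. Whole-arm comparisons.** At the planning rates in Sample size (70% opt-in, 80% opt-out participation), about 70% of opt-in households and 100% − 80% = 20% of opt-out households fall under the named-parent rule. The difference is 50 points, so any effect on a whole-arm comparison is about half that among consenters.

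**3. Numbers available.** The article gives no figure for this effect to reproduce. Its interview flow is consistent: 1,026 + 57 + 13 + 28 + 5 = 1,129. With 1:1 allocation there are 1,129/2 = 564.5 households per arm. Applying the planning rates and the 91% interviewed:
- opt-in consenters: 564.5 × 0.70 × 0.91 ≈ 360
- opt-out consenters: 564.5 × 0.80 × 0.91 ≈ 411

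**4. Illustration. The mix and gap values are assumptions; the documents give neither.**

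Spurious difference = (difference between rules in the share of one respondent type) × (gap between respondent types on the item).

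For an item with 50% prevalence, SE = √[0.25 × (1/360 + 1/411)] ≈ 0.036. The true type I error of a nominal two-sided 5% test is 1 − Φ(1.96 − d/SE) + Φ(−1.96 − d/SE), where d is the spurious difference.

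| Mix difference | Gap | Spurious difference | True type I error |
|---|---|---|---|
| 0 points | any | 0 | 0.050 |
| 5 points | 10 points | 0.5 points | 0.052 |
| 10 points | 20 points | 2 points | 0.086 |
| 20 points | 20 points | 4 points | 0.198 |
| 30 points | 30 points | 9 points | 0.70 |

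For whole arms the same assumptions give 0.25 to 4.5 points and a type I error of about 0.051 to 0.30.

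**5. Partial interviews.** The 101 partial interviews usually answered only the question on reasons, so other items rest on the 82% who completed: about 324 and 370 consenters. The 4-point case then gives 0.183 instead of 0.198, which is little different.

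**The case against.** **Both rules may often reach the mother.** The letter was addressed to her. The hospital listings held her mobile and landline numbers and only often a partner's mobile. If the same parent is reached either way, the bias is small. This stands, and it is why no size can be claimed.

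**Selection bias is already protected.** The Discussion says it can be assessed from hospital records on all mothers, whatever was answered at interview. This stands for the characteristics held there: age, marital status, country of birth, Indigenous status, location and area disadvantage. It does not cover education and main language, which are listed for the interviewee only, nor reasons, recall, knowledge, trust and preferences.

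**A larger false difference might be inferred than the documents support.** Suppose 60% of parents who read the leaflet and 20% of those who did not answer a knowledge item correctly, and 10% to 40% of first-answerers had not read it. The gap is then 0.10 × 40 = 4 to 0.40 × 40 = 16 points. With 360 and 411 consenters, z is about 1.1 at 4 points, 2.2 at 8 and 4.5 at 16. These inputs are assumed, and the sum treats every non-reader as an artefact. In some households nobody read the material. They are included through inertia, which the Background names as a feature of opt-out consent, so their lower knowledge is a real consequence of the method. Only households where the other parent read or decided contribute to the artefact, and that share is not given.

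**The stated reason might be read as contradicting the protocol,** since the mother was the addressee and the unit of randomisation. It does not: the reason concerns who had read the material, and neither fact settles that.

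**An article may leave this to the full analysis plan.** A sensitivity analysis could well be there. But the article itself fixes the two rules and the hypotheses, and the near-aliasing follows from those.

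**Conclusion.** The concern holds as a limit on interpreting the interview-based secondary comparisons. The documents establish the structure: within consent strata, the respondent-selection rule is nearly aliased with arm, and the stated adjustment does not address it. They do not establish that the comparisons are in fact biased, in which direction, or by how much. Parent mix and proxy counts by arm are not given. The 0.5 to 9 points among consenters (0.25 to 4.5 for whole arms) rest on assumed mix differences of 5 to 30 points and gaps of 10 to 30 points, with zero at no mix difference.

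The primary participation comparison and the hospital-record maternal characteristics are untouched. A reader might infer that consenters in the two arms are simply different kinds of parent, or that any interview difference is an artefact. Neither follows: the named parent was not always reached, and both rules may mostly yield mothers.

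**What to change.** 1. Make the between-arm socio-demographic comparison of consenters on the mother-level and household-level variables listed in Outcome assessment and Discussion, not on the interviewee's own age, gender and education.
2. Tabulate respondent type by arm and consent status: mother or father; and named on the form, proxy, or first to answer. Adjust the interview-based secondary models for mother or father, and add a sensitivity analysis restricted to mothers' interviews.
3. State that residual confounding by the respondent-selection rule limits interpretation of these comparisons.

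The mothers-only analysis is better kept as a sensitivity analysis than made the main one. It drops fathers who signed, who are the right respondents on reasons, and it does not fully remove the aliasing, because a mother in a non-reply household enters only if she answered first. The main models should not adjust for recall or reading of the material: it is a post-randomisation outcome, and adjusting for it can remove real effects of the consent method.

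The cost is a little more analysis and lower precision in the mothers-only results. Interviewee gender is already recorded and the article says analysis has not begun, so nothing further is needed from parents.
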